### 3.4. Correlation analysis of the microbiome and metabolome

Spearman's rank correlation coefficient will be calculated for all ASV-metabolite pairs and clinical parameters using the data across the same samples. A network analysis is to be performed on the interaction matrix using the fast greedy community algorithm in the igraph R package. This algorithm identifies subgraphs using direct optimization of a modularity score. Each discovered community is annotated according to the KEGG pathways of the metabolites within the community.

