**Expected outcomes:**

The change in the severity of the tic disorder is set as the main outcome. Secondary outcomes include gastrointestinal severity index and recurrence rate, which will be calculated after a 12-week follow-up. Gut microbiota, measured by 16S rRNA gene sequencing; serum metabolomics, assessed *via* LC/MS; and serum zonulin, assessed by enzyme-linked immunosorbent assay (ELISA), will be used as biological specimen analysis outcomes. The present study will investigate the possible interactions between intestinal flora and serum metabolites and the improvement of clinical profiles, which may elucidate the mechanism of Qihuang needle therapy for tic disorders.

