Most studies regarding the mechanism of acupuncture therapy for tic disorders are conducted *via* animal model experiments, which focus on acupuncture regulating neurotransmitters (32, 33). Studies investigating the mechanism in the clinical context are insufficient. Recently, omics analyses have been used as prospective methods to probe acupuncture mechanisms in the clinical context. Using gut microbiome sequencing, acupuncture was found to modulate the structures and diversity of the gut microbiome, inhibit inflammation of the central nervous system (34, 35), gradually improve gut barrier function, and regulate neurotransmitters (36, 37) in various neuropsychiatric diseases. As for metabolomics assays, the potential mechanisms of acupuncture to treat neuropsychiatric disorders may be associated with modulating systematic inflammation and improving lipid metabolism (38–40). QHN therapy shows effectiveness in the treatment of tic disorders in clinical practice and is worth investigating to determine the specific mechanism. Nevertheless, omics studies of tic disorders are in their infancy (25, 41), with few studies on acupuncture. We aimed to determine how QHN therapy works in the treatment of tic disorders by investigating how it influences the gut microbiota and serum metabolites in children with tic disorders and to analyze possible correlations between clinical profiles and the changes in the gut flora and serum metabolites.

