### 2.5. Outcome evaluations

The clinical evaluations include the assessment of the severity of tics and gastrointestinal symptoms. The recurrence rate will be measured after a 12-week follow-up. The primary outcome measure will be the Yale Global Tic Severity Scale (YGTSS), and secondary outcomes will consist of the gastrointestinal severity index (GSI) and the recurrence rate. Biological specimen analysis outcomes will include changes in the composition of intestinal microbiota, serum metabolites, and serum zonulin. YGTSS and GSI will be assessed at baseline and after 4 weeks when the interventions have been completed. Data relating to the recurrence rate will be collected after a 12-week follow-up. Feces and serum samples will be collected at baseline and 4 weeks after the interventions. If sample collection is concurrent with a treatment, sample collection will be performed after all interventions have been completed. The feces sample will be collected as soon as possible after completing all interventions.

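### The aim is to correlate clinical profiles with changes in flora and metabolites, but the only correlation rule uses per-sample values, with no change score and no limit by group or visit

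*Protocol article*

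**What the plan says.** Three places in the protocol article put the interest in change. The Introduction states the aim "to analyze possible correlations between clinical profiles and the changes in the gut flora and serum metabolites". The abstract, under Expected outcomes, refers to "possible interactions between intestinal flora and serum metabolites and the improvement of clinical profiles". Section 2.5 says: "Biological specimen analysis outcomes will include changes in the composition of intestinal microbiota, serum metabolites, and serum zonulin".

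Section 3.4 gives the only correlation method: "Spearman's rank correlation coefficient will be calculated for all ASV-metabolite pairs and clinical parameters using the data across the same samples". The resulting interaction matrix goes to a network analysis "using the fast greedy community algorithm in the igraph R package", which section 3.4 describes as optimising a modularity score. Each community found is then annotated with KEGG pathways.

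On timing, section 2.5 says "YGTSS and GSI will be assessed at baseline and after 4 weeks when the interventions have been completed" and, for specimens, "Feces and serum samples will be collected at baseline and 4 weeks after the interventions". It adds that a sample falling together with a treatment is taken once all interventions are finished, and that feces are collected as early as possible after that.

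**The concern.** A correlation of levels asks whether children, or samples, with more of a taxon also have more of a metabolite or worse tics. A correlation of changes asks whether children whose taxon moved more also had metabolites or tic scores that moved more. The Introduction asks the second question and section 3.4 calculates the first.

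The sample set makes this matter more. Section 2.5 gives two collection times, and section 2.1 gives two groups, patients and untreated healthy children. Section 3.4 does not say which of these samples enter a coefficient. If they are combined, two distortions follow:

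- Two samples from one child count as two independent observations.
- Any two features that both differ between patients and controls become correlated, even if they are unrelated within each group.

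The links between microbes, metabolites and symptoms carry the mechanistic claim of the study. Under pooling, part of that network would show repeat sampling and case-control differences rather than features that move together within a child.

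**Working it through.** **Inputs from the protocol article.** Section 2.3: at least 15 per group, 20% dropout, 20 per group recruited. Section 3.1.1: two-sided 0.05. That level is stated for the clinical data and zonulin; using it for the correlations is an assumption, because section 3.4 gives no threshold.

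**Assumed inputs.** Within-child intraclass correlation (ICC) 0.3-0.7 for each feature; group difference in both features 0 to 1.0 SD. The article gives neither.

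**The plan's own figure.** 15/(1 - 0.20) = 18.75, rounded up to 19 per group; the plan recruits 20, which is close. With 20% dropout, 20 × 0.8 = 16 remain. No figure is given for the correlation analysis.

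**Step 1: repeat samples.** Take two unrelated features, each with intraclass correlation ICC, and two samples per child treated as independent. The variance of the sample correlation is inflated by about 1 + ICC². The false-positive rate is then about 2 × [1 - Φ(1.96/√(1 + ICC²))].

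| ICC | √(1 + ICC²) | Approximation | Simulated, n = 15 and 20 |
|---|---|---|---|
| 0.3 | 1.044 | 6.0% | 5.8-6.3% |
| 0.5 | 1.118 | 8.0% | 7.4-7.5% |
| 0.7 | 1.221 | 10.8% | 10.6-11.1% |

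Each simulated rate rests on 4,000 runs of Spearman's test. Across repeated simulations the range for ICC 0.3-0.7 is about 5-11%.

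**Step 2: adding controls.** Let a fraction p of the samples come from patients, and let both features differ by d SD between groups with no association within either group. The pooled correlation is about p(1 - p)d²/[1 + p(1 - p)d²]. With patient pre, patient post and control samples in equal numbers, p = 2/3 and p(1 - p) = 2/9:

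- d = 0.8: 0.142/1.142 = 0.12
- d = 1.0: 0.222/1.222 = 0.18

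A coefficient that should be zero is therefore centred above zero. Simulated false-positive rates with 20 per sample set are about 6-8% at d = 0, about 16-20% at d = 0.8 and about 30-31% at d = 1.0.

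**Step 3: other ways of pooling.**

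- Baseline samples only, both groups: 6.4-6.7% at 0.5 SD, 12-14% at 0.8 SD, 20-24% at 1.0 SD.
- Both groups sampled twice, ICC 0.5: 11%, 22-26% and 35-44% at the same differences.
- Patients only, both visits, ICC 0.5, with a mean treatment shift in both features: 8.1-8.4%, 12.6-14.5% and 21-26% at 0.5, 0.8 and 1.0 SD.

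**Step 4: the alternative.** Spearman on post minus pre, one value per patient, gives 5.0% at n = 15 and at n = 20, even with a mean shift of 0.8 SD in both features. One group at one visit also holds its level (5.3% and 4.8%).

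**Step 5: precision of the alternative.** The rho detectable with 80% power for a single pair is tanh[(1.960 + 0.842) × √(1.06/(n - 3))]:

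- n = 16: tanh(2.802 × 0.2856) = 0.66
- n = 20: tanh(2.802 × 0.2497) = 0.60

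After multiplicity control the bar is higher. At n = 16 (t approximation, 14 df), p = 10⁻⁴ needs |rho| of about 0.82 and p = 10⁻⁶ about 0.91.

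**The case against.** **Pooling is not stated.** The phrase about the same samples may mean only that microbiome, metabolome and clinical values are matched by specimen. The handling of visits and groups is detail that an article often leaves to the full plan. A reader might infer that the study will stack all samples as independent; the text does not say so, and the rates above are conditional on it. What remains is that, even on the benign reading, section 3.4 gives correlations of levels while the Introduction asks about changes.

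**Level correlations have a purpose.** The Discussion (section 5) also looks for links between tic-associated metabolomes and tic-linked microbiomes. Levels serve that aim. This stands, so section 3.4 is incomplete for one aim rather than wrong for all.

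**The sizes depend on assumptions.** At low ICC with no group difference the inflation is about one percentage point. Under pooling its direction does not depend on the chosen values; its size does.

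**Symptom links.** A reader might extend the case-control figures to YGTSS and treat that score as a group label. The article does not clearly say that controls are scored, and section 3.1.1 analyses YGTSS and GSI in the experimental group only. The figures with controls therefore apply to ASV-metabolite pairs.

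**Network algorithm.** A reader might infer that the community step is invalid on signed coefficients or runs on the unfiltered matrix. Section 3.4 states neither, and the first would need software facts from outside the article.

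**Timing.** A reader might infer that specimens are taken four weeks after treatment ends, and so after the YGTSS visit. The other sentences of section 2.5 point to the end of treatment. What is left is ambiguous wording.

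**Conclusion.** The concern holds in a limited form. The stated aim concerns changes, and the stated correlation method uses per-sample values without a change score or any restriction by group or visit. Followed as written, it does not answer that aim.

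The wording also leaves open a pooled analysis. Under it, a nominal 5% error rate would become about 5-11% (patient visits pooled), about 6-8% (controls added, no group difference) or about 16-31% (both features differing by 0.8-1.0 SD). These figures assume the ICC and SD values given, a two-sided 0.05 threshold and three sample sets of 20. They show what the text permits, not what it commits to. The timing sentences in section 2.5 are a minor point of wording.

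**What to change.** 1. For the change aim, state that Spearman coefficients are calculated between within-patient changes (post minus pre) in taxa, metabolites and YGTSS/GSI, in the experimental group only.
2. For the disease-association aim of the Discussion, report level correlations separately by group and by visit.
3. Build the network from edges that survive multiplicity control. Compare its modularity with a permutation null, because an algorithm that optimises modularity returns a partition whether or not there is structure.
4. Reconcile the sentences on specimen timing in section 2.5 with each other and with the YGTSS visit.

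No new patients or samples are needed. The cost is precision: with 16-20 patients only a rho of about 0.60-0.66 is detectable for a single pair, and after multiplicity control the network may be sparse or empty. It should be reported as exploratory. There is also no untreated patient group, so correlated changes would describe features moving together over the treatment period and could not be attributed to the treatment.

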## 1. Introduction

Tic disorders are neurodevelopmental disorders characterized by recurrent motor and/or vocal tics (1). The Diagnostic and Statistical Manual of Mental Disorders, Fifth Edition (DSM-5) (2), defines the following five tic disorders: provisional tic disorder; persistent (chronic) motor or vocal tic disorder; Tourette's disorder (also known as Tourette's syndrome [TS]); other specified tic disorder; and unspecified tic disorder. Tic disorders are common in China, with a prevalence of transient tic disorder (TTD), chronic tic disorder (CTD), and Tourette syndrome (TS) of 1.7, 1.2, and 0.3%, respectively (3).

Tics usually begin between the ages of 3 and 8 years and become worse between the ages of 8 and 12 years for most patients. The first tic symptoms are usually simple motor tics, restricted to one muscle or a single muscle group. Tics then progress to involve more muscle groups or present with mimicking. Simple vocal tics, demonstrating meaningless sounds, usually occur after motor tics. For children or adolescents, the features of tics wax and wane in severity and frequency, and new tic symptoms replace, combine with, or even exacerbate the old ones (4, 5). Academic stress and family pressure may increase the incidence of tic disorders among school-age children. Excessive attention from parents, ridicule from peers, or incomprehension from teachers contribute to the aggravation of tics. Despite reports that tics tend to mitigate spontaneously throughout adolescence and reach complete remission in early adulthood, tics do not always remit within a year in most children with recent-onset tic disorders, and recurrence may occur even after long-term remission among patients with CTD (6). Attention-deficit hyperactivity disorder, obsessive-compulsive disorder, and autism spectrum disorder are the most common psychiatric comorbidities that impair social, behavioral, or emotional functioning (7).

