### 2.2. Eligibility criteria

Participants must fulfill the diagnostic criteria for provisional tic disorder and persistent motor or vocal tic disorder according to the DSM-5 (2). Patients will be screened according to the inclusion and exclusion criteria listed in Table 1.

**Table 1 T1:** Eligibility criteria.

	**TD patients**	**Healthy controls**
Inclusion Criteria	1. Aged between 4 and 18 years	1. Matched age, sex, family history of a psychiatric condition, parental marital status, mode of delivery and birth weight to the TD group^*^
	2. Meeting the diagnostic criteria of transient tic disorder and Persistent Motor or Vocal Tic Disorder according to the Diagnostic and Statistical Manual of Mental Disorders, Fifth Edition (DSM-5) (1, 2)	2. No current or history of head trauma, convulsions, epilepsy, growth and development disorders, mental illness, digestive system disease, abdominal operation or asphyxia at birth
	3. The course of a provisional tic disorder is more than 3 months	3. No current or history of medication of mental disorders especially drug influencing neurotransmitters
	4. The score of YGTSS >12	4. The mother is healthy during pregnancy (no history of infection, digestive system disease, trauma or taking any medication)
	5. Have not received acupuncture or moxibustion within 3 months, and drug withdrawal period ≥12 weeks	
	6. Guardians are willing to sign the informed consents	
Exclusion Criteria	1. Secondary tic disorders	
	2. Patients with severe diseases of important organ systems: liver and kidney damage, cardiovascular insufficiency, metabolic diseases, malignant tumors, etc., which may adversely affect our clinical observation	
	3. Obsessive-compulsive disorder, depression, Attention deficit hyperactivity disorder, anxiety, autism spectrum disorder, eating disorder, or a history of substance abuse	
	4. Epilepsy, Huntington's disease, rheumatic chorea, hepatolenticular degeneration, substantia nigra degeneration, psychogenic tics and other extrapyramidal disorders	
	5. The use of antibiotics, probiotics, high-dose vitamin or immunomodulatory medications within 4 weeks before the fecal sample collection	
	6. Conditions like any infective diseases or other severe disorders that may influence the gut microbiota	
	7. Ulcers or surgical scars on the acupoint area	
	8. Children who are participating or participated in other clinical trials within 1 month	

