Withdrawal criteria and management	1. Misdiagnosis, violation of the inclusion criteria	
	2. Self-use of prohibited treatment	
	3. Poor cooperation with the established treatment or data collection procedures	
	4. Serious adverse events or life-threatening diseases or an acute progression of the disease occurs during the trial	
	5. Obvious discomforts arise because of the therapy	
	6. Participants request withdrawal voluntarily	

American Psychiatric Association (1).

* Healthy control matching procedure: To select a healthy control group comparable in size to the experimental group. The criteria used for this procedure (with match tolerance) are as follows: (1) age (±1 year), (2) sex (exact match), (3) family history of the psychiatric condition (exact match), (4) parental marital status (exact match), (5) mode of delivery (exact match), and (6) birth weight (±100 g). We chose to match these variables as they may be the risk factors influencing the development of tic disorders.

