### 3.1. Statistical analysis

#### 3.1.1. Clinical data and serum zonulin

For the clinical data, statistical analyses will be performed using SPSS Statistics 24.0 (IBM SPSS Statistics, Armonk, NY). Children in the experimental group will be matched to their peers in the healthy control group on age, sex, family history of a psychiatric condition, parental marital status, mode of delivery, and birth weight. Categorical variables will be described in the form of frequencies or percentages. Continuous variables will be presented as mean ± standard deviation or median and range. The chi-square test or Fisher's exact test will be used to compare the change in the categorical variables. Changes in YGTSS, GSI, and concentration of serum zonulin in the experimental group before and after treatment will be analyzed using paired sample *t*-test if the data conform to a normal distribution. The Wilcoxon paired-samples signed-rank test will be performed if the data do not conform to normal distribution or if there are differences in variance uniformity. Differences in concentration of serum zonulin between two matched groups at baseline will be analyzed with the above statistical methods. The results are based on two-sided tests, and a *P*-value of <0.05 will be considered statistically significant.

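### Section 3.4 correlates flora, metabolites and clinical measures without adjusting for age across ages 4 to 18, so ASV-metabolite pairs that both depend on age can appear as network links

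*Protocol article*

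**What the plan says.** Section 3.4 names the statistic and its scope. Spearman's "rank correlation coefficient will be calculated for all ASV-metabolite pairs and clinical parameters using the data across the same samples" will be obtained, a community-detection algorithm will run on the resulting matrix, and each community will be annotated with KEGG pathways. No covariate, partial coefficient or age stratum appears there or elsewhere in the analysis text (sections 3.1 to 3.4).

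On age, Table 1 admits patients "Aged between 4 and 18 years". Age is handled only by the pairing of groups: section 3.1.1 has patients "matched to their peers in the healthy control group on age, sex" and further variables, and the footnote to Table 1 sets the age tolerance at 1 year either way. The footnote gives the reason: "We chose to match these variables as they may be the risk factors influencing the development of tic disorders". It does not mention age effects on flora or serum metabolites.

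The Introduction describes tics that "become worse between the ages of 8 and 12 years for most patients", and cites reports that "tics tend to mitigate spontaneously throughout adolescence". It also states the aim served by the correlations: "to analyze possible correlations between clinical profiles and the changes in the gut flora and serum metabolites".

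**The concern.** Matching and adjustment do different jobs. Matching on age makes the patient and control age distributions alike. A correlation across children, whether in one group or both, still uses the full age spread of those children. If an ASV rises with age and a metabolite also rises with age, the two correlate even when neither affects the other.

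The problem arises with one sample per child from a single group, so it is separate from any question about pooling visits or groups. False-discovery control would not remove it, because the marginal correlation is real; only its reading as a direct link is wrong.

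At stake is the interpretation of the network. Features that share one common cause are mutually correlated, so they can be grouped into one community and given a KEGG label. The Discussion expects these correlations to help explore a molecular mechanism of tic disorders.

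**Working it through.** **Inputs from the protocol article.** Age 4 to 18 years (Table 1). 20 children per group planned, with 20% dropout allowed (section 2.3), so 20 × 0.8 = 16 remain per group. Plain Spearman coefficient (section 3.4). The article states no figure for this analysis, so there is none to reproduce.

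**Assumptions.** The documents do not give the strength of age dependence, so it is varied. An ASV and a metabolite each correlate with age at a, and are independent given age. Age is uniform on 4 to 18. A two-sided nominal P<0.05 serves as a yardstick, since section 3.4 sets no rule for which coefficients count.

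**Induced correlation.** With no direct link, the Pearson correlation between the two features is a × a = a². Under normality, the Spearman value is close to (6/π) × arcsin(a²/2):
- a = 0.3: a² = 0.09, rho about 0.09
- a = 0.4: a² = 0.16, rho about 0.15
- a = 0.5: a² = 0.25, rho about 0.24
- a = 0.6: a² = 0.36, rho about 0.35

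The simulated means agree (0.08, 0.15, 0.24, 0.35).

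**How often such a pair looks significant** (simulation, 20,000 runs per setting when rechecked, rounded):

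| Correlation of each feature with age | Induced rho | n = 16 | n = 20 |
|---|---|---|---|
| 0.3 | 0.08 | 6% | 6.5% |
| 0.4 | 0.15 | 8% | 10% |
| 0.5 | 0.24 | 14% | 18% |
| 0.6 | 0.35 | 27% | 34% |

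The reference value is 5%. Replacing the plain coefficient with a Spearman coefficient partial on age and sex gives 5% to 6% in every one of these settings.

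**Where the effect is smaller.**
- Narrower ages: with the same slope per year but ages uniform on 6 to 12, the n = 20 rate is 5% to 6.5% for a from 0.3 to 0.6, and 9% at 0.7.
- Tic scores: a score that peaks at age 10 and falls on both sides, set against a feature monotone in age, gives a mean rho between -0.03 and -0.18 and a rate of 5% to 13% at n = 20, for a from 0.3 to 0.7. For an ASV-metabolite pair at 0.7 the rate is 62%.
- Changes: let x1 = g(age) + e1 before treatment and x2 = g(age) + e2 after it. Then x2 - x1 = e2 - e1, and the stable age term cancels. Age matters for changes only if the response itself varies with age.

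**The case against.** A reader might infer that flora, metabolites and tic scores are known to vary with age here, so that the network will be largely an age artefact. The documents do not support that.

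- They nowhere say that flora or metabolites depend on age. The strength is an assumption, and at 0.3 the inflation is negligible. This stands, and is why a range is given.
- The one age pattern they do describe, for tics, rises and then falls. A rank correlation picks up little of it unless enrolled ages lie mainly on one side of the peak. This stands: YGTSS correlations are less exposed than ASV-metabolite pairs.
- The Discussion says most patients are school-aged, so actual ages may be narrower than the eligibility range. This reduces the figures, but Table 1 sets no narrower limit.
- The stated aim refers to changes, in which stable age differences largely cancel. Section 3.4 does not say whether levels or changes enter the matrix, so this cannot be relied on, but it may remove much of the problem.
- Section 3.4 sets no P<0.05 threshold. The induced rho is therefore the more direct measure, and the percentages are only a yardstick.
- The work is exploratory, the article condenses a fuller protocol, and covariates are often left to an analysis plan. That excuses omitted detail. Here, however, the article does state the coefficient, algorithm and annotation step, and a better coefficient is available from data already recorded.

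Larger figures can be produced with 40 children, but they require both groups to be pooled, which section 3.4 does not state. They are not relied on here.

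**Conclusion.** The point holds in a limited form. The planned coefficients are unadjusted, eligible ages run from 4 to 18, and matching within 1 year does not remove the age spread among the correlated samples. ASV-metabolite pairs that both depend on age can therefore appear as links. In a single group of 16 to 20 children the effect runs from negligible (age correlation 0.3) to material (0.6, where 27% to 34% of such pairs reach nominal significance). These sizes assume monotone age dependence of equal strength in both features, ages spread evenly over the eligible range, and correlation of levels. They apply only to pairs in which both features depend on age, not to all pairs in the matrix. The sample size is not affected. This is an inexpensive improvement worth making, not a flaw that invalidates the plan.

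**What to change.** In section 3.4, specify Spearman coefficients partial on age and sex: rank each variable, regress the ranks on age (ranked) and sex, and correlate the residuals. Build the network from these coefficients and keep the unadjusted matrix as a sensitivity display. State in the same section whether levels or before-after changes are correlated, and which groups and visits enter the matrix.

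The reasoning above concerns age. Sex is included because it is also a recorded matching variable and can be adjusted for in the same step; the documents give no evidence on its effect.

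The cost is a sentence or two of text and two degrees of freedom per coefficient: the residual degrees of freedom fall from n - 2 to n - 4, that is from 18 to 16 with 20 children and from 14 to 12 with 16. Both variables are already collected, and design, recruitment and sample size do not change.
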